### Eligibility criteria

Patients with PCS and cognitive deficits will be recruited from the specialised outpatient clinic of the Department of Neurology at Charité. Inclusion and exclusion criteria for the trial population are comprehensively outlined in Table 2. Informed consent from all participants is mandatory and will be documented after the screening visit, ensuring at least a 24-h period before baseline 1.

**Table 2 Tab2:** Inclusion and exclusion criteria for trial population

*Inclusion criteria*
1. History of confirmed (PCR or serology) SARS-CoV-2 infection according to WHO criteria
2. Ongoing symptoms of PCS for ≥ 3 months
3. Self-reported predominant cognitive deficits at screening
4. Male or female adult who is 18 years or older at the time of informed consent
5. Subject is willing, understanding, and able to provide informed consent
6. Signed informed consent prior to initiation of any trial related measure
7. For female subject or diverse subjects:
(a) Confirmed post-menopausal state, defined as amenorrhea for at least 12 months, or
(b) If being of childbearing potential:
1. Negative highly sensitive urine or serum pregnancy test before inclusion, and
2. Practicing a highly effective birth control method (failure rate of less than 1%):
(a) combined (oestrogen and progestogen containing) hormonal
(b) contraception associated with inhibition of ovulation (oral/intravaginal/ transdermal), or
(c) progestogen-only hormonal contraception associated with inhibition of ovulation (oral/injectable/implantable), or
(d) Intrauterine device, or
(e) Intrauterine hormone-releasing system, or
(f) Bilateral tubal occlusion, or
(g) Vasectomised partner, or
(h) Heterosexual abstinence
*Exclusion criteria*
1. Any ongoing central nervous system disease
2. Any major psychiatric disease within the last 10 years
3. Previous medical history of gastric ulcer, osteoporosis and/or previous vertebral fractures, rheumatological disease or metabolic disease including diabetes mellitus
4. Ongoing immunosuppressive therapy
5. Patient is pregnant or breastfeeding at screening
6. MMQ memory satisfaction subdomain > 50 points at Screening
7. Current malignant disease (including space-occupying brain tumours)
8. Body weight < 45 kg
9. Severe lactose intolerance
10. Participation in another clinical interventional trial within the last 3 months or five half-lives of the other trial’s IMP, if longer than 6 months previous to informed consent
11. Patient is institutionalized by order of court or public authority
12. Patient who might be dependent on the sponsor, the investigator or the trial site
13. Place of living does not allow the subject to attend the planned study visits
14. Other conditions that are likely to affect the safety of the study treatment (e.g., severely impaired immune status)
*Additional exclusion criteria for MRI assessments*
1. Pacemaker
2. Metal implants and other objects that are not proven MRI safe (e.g., drug pumps, heart valves, shards, joint prosthesis, hearing aids, stents)

IMP, Investigational medicinal product; MMQ, Multifactorial Memory Questionnaire; MRI, magnetic resonance imaging; PCR, Polymerase chain reaction; PCS, Post-COVID-19 syndrome; SARS-CoV-2, Severe acute respiratory syndrome coronavirus 2; WHO, World Health Organization

### Arms and intervention

Participants will be stratified based on age (> 50 years or ≤ 50 years), sex and cognitive screening assessment results, as determined by the MoCA at baseline 2 (> 26/30 or ≤ 26/30 points). Randomization will occur in a 1:1 ratio, assigning participants to either the verum or placebo group. The total intervention duration per participant is 20 weeks. The initial six weeks constitute a double-blind intervention with a starting dose of body weight-adjusted methylprednisolone or matching placebo. In the verum group, participants receive oral methylprednisolone at a dose of approximately 1 mg/kg body weight, taken once daily for four weeks followed by a two-week tapering phase. Conversely, in the control group participants receive a matching placebo orally once daily for six weeks, adhering to a comparable titration schedule to maintain blinding. Following the initial six-week blinded intervention, a drug-free period of six weeks ensues. This is followed by a second, unblinded treatment phase lasting the same duration with an equivalent tapering scheme. During this phase, all participants receive methylprednisolone Three follow-up visits (week 8, week 20, and week 52) are scheduled in addition to the six safety visits.

### Outcome measures

The primary outcome measure is the intra-patient change in the MMQ sub-domain memory satisfaction, demonstrating an increase of ≥ 15 points from baseline to week 8 [25]. Key secondary and safety outcome measures include: (a) Intra-patient change in MMQ sub-domain memory satisfaction from baseline to week 20 and week 52, along with changes from week 8 to week 20, and from week 20 to week 52 (b). Mean difference in MMQ sub-domain memory performance and memory strategy from baseline to week 8, (c) Intra-patient change in neuropsychological and cognitive scores and quality of life measures from baseline to week 8 and week 20, and from week 8 to week 20 (d). Exploratory biomarker-related outcomes encompass the occurrence and change in molecular biomarkers in serum and CSF as well as structural or functional alterations in imaging of cortical and subcortical regions and fibre tracts implicated in neurocognitive processes.

The assessment of investigational medicinal product side effects is conducted through adverse event, serious adverse event, and suspected or unexpected serious adverse reaction reports. Detailed objective measures and outcomes are shown in Table 3.

**Table 3 Tab3:** Objectives and Outcomes

Objective	Outcome
*Primary*	
Improvement in memory satisfaction from baseline to week 8 when comparing methylprednisolone with placebo in PCS patients	Intra-patient change in MMQ subdomain memory satisfaction by ≥ 15 points from baseline to week 8
*Secondary*	
Long-term improvement in memory satisfaction from baseline to week 20 and to week 52	Intra-patient change in MMQ subdomain “memory satisfaction” from baseline to week 20, from week 8 to week 20 and from week 20 to week 52
Improvement in memory ability, and memory strategy	Mean difference in MMQ subdomain “memory ability” from baseline to week 8 and to week 20 and from week 8 to week 20
Mean difference in MMQ subdomain “memory strategy” to week 8 and to week 20 and from week 8 to week 20	
Improvement in neurocognitive symptoms quantified using neuropsychological and cognitive scores	Intra-patient change in neuro-psychological and cognitive scores (MoCA, neuropsychological test battery, SDMT) from baseline to week 8 and to week 20 and from week 8 to week 20
Improvement in quality of life	Intra-patient change in quantified PROMIS questionnaire and SF-36 from baseline to week 8 and to week 20 and to week 52 and from week 8 to week 20
Improvement in fatigue and mood	Intra-patient change in fatigue scores (FSS, CFQ) and mood (BDI) from baseline to week 8 and to week 20 and to week 52 and from week 8 to week 20
*Key safety*	
Infections meeting SAE criteria	Occurrence of IMP side and adverse effects, assessed with AE, SAE and SUSAR reports
Psychiatric complications (depression, euphoria, severe sleep disorders)	
Endocrinologic disorders meeting SAE criteria	
*Exploratory*	
Biomarker-related: Autoimmune activity, immune status, inflammatory biomarkers, complement system	Occurrence and changes in molecular biomarkers
Biomarker-related: Structural changes in the brain and in brain functions	Structural and functional alterations in MRI imaging in cortical and subcortical regions and fibre tracts with relevance to neurocognitive processes

AE, adverse event; BDI, beck depression inventory II; CFQ, chandler fatigue scale; FSS, fatigue severity scale; IMP, investigational medicinal product; MMQ, Multifactorial Memory Questionnaire; MoCA, Montreal Cognitive Assessment; MRI, magnetic resonance imaging; PROMIS, patient reported outcomes measurement information system; SAE, serious adverse event; SDMT, symbol digit modalities test; SF-36, Short form 36 health survey; SUSAR, Suspected unexpected serious adverse reaction

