**Fig. 1 Fig1:**
[figure not shown]
Flowchart of the post-corona-virus immune treatment (PoCoVIT) trial

Eleven trial visits, detailed in Table 1, including screening, are planned for each patient. The total trial duration for each participant is one year, including two treatment phases, each consisting of 4 weeks of treatment followed by 2 weeks of tapering.

**Table 1 Tab1:** Visit schedule with assessments

Period/Visit name	Screening	Baseline 1	Baseline 2 &Randomization	Treatment period: Placebo vs Verum^1^			Follow-Up	Treatment period: Verum^2^			Follow-Up	
	S (V1)	B1	B2 (V2)	SV (V3)	SV (V4)	SV (V5)	FU1 (V6)	SV (V7)	SV (V8)	SV (V9)	FU2 (V10)	FU3 (V11)
Trial days	− 28 to 0		− 14 to 0	2	14	28	56	86	98	112	140	365
Time windows	± 3 days											± 30 days
Outpatient visit	•		•	•	•	•	•	•	•	•	•	
Informed consent	•											
Inclusion and exclusion criteria	•											
Randomization			•									
Discharge from trial											•	
*History*												
Demographic data			•									•
Medical history			•									
*Diagnostic assessments*												
Structural cMRI		•										
Diagnostic blood sample^3^			•				•				•	
Lumbar puncture^4^			•									
*Safety assessments*												
Neurological and general physical examination			•				•				•	
Pregnancy test in female patients			•		•		•		•		•	
Blood sample A^5^				•	•	•		•	•	•		
Blood sample B^6^			•				•				•	
Clinical and sonographic exclusion of thrombosis					•				•			
AE questioning			•	•	•	•	•	•	•	•	•	
Concomitant medication			•	•	•	•	•	•	•	•	•	•
*Outcome assessments*												
Patient reported symptoms			•				•				•	•
Multifactorial Memory Questionnaire			•				•				•	•
Short form 36 Health survey			•				•				•	•
Fatigue severity scale			•				•				•	•
Chalder fatigue scale			•				•				•	•
Beck depression inventory-II			•				•				•	
Montreal cognitive assessment			•				•				•	
PROMIS 29			•				•				•	
PROMIS Cognitive Function Short form 4a			•				•				•	
Verbal learning and memory test			•				•				•	
Brief Visuospatial memory test—revised			•				•				•	
WAIS-IV			•				•				•	
Test battery for attention performance			•				•				•	
Trail-making-test A and B			•				•				•	
Regensburger Wortflüssigkeits-test			•				•				•	
Symbol digit modalities test			•				•					
Wortschatztest			•									
LPS			•									
Assessment of self-experienced exposure to IMP						•						
Enrolment in diagnostic and biomarker platform study in a subgroup			•				•					

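### Tables 1 and 3 contradict each other for three secondary outcomes: SDMT at week 20, and PROMIS and BDI at week 52, are defined as outcomes but never scheduled

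*Protocol article*

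**What the plan says.** Table 3 (Objectives and Outcomes) sets these secondary outcomes:

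- Cognition: change in "MoCA, neuropsychological test battery, SDMT) from baseline to week 8 and to week 20 and from week 8 to week 20".
- The PROMIS and SF-36 row: "Intra-patient change in quantified PROMIS questionnaire and SF-36 from baseline to week 8 and to week 20 and to week 52", plus the interval between weeks 8 and 20.
- The FSS, Chalder and BDI row: "Intra-patient change in fatigue scores (FSS, CFQ) and mood (BDI) from baseline to week 8 and to week 20 and to week 52", plus the interval between weeks 8 and 20.

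Table 1 (Visit schedule with assessments) has these rows:

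- "Symbol digit modalities test" is marked at baseline 2 (B2) and follow-up 1 (FU1, day 56) only.
- "Beck depression inventory-II", PROMIS 29 and "PROMIS Cognitive Function Short form 4a" are marked at B2, FU1 and follow-up 2 (FU2, day 140). Follow-up 3 (FU3, day 365) is empty for all three.
- Lumbar puncture is marked at B2 only, and the Trial description and design section makes CSF sampling optional. "Structural cMRI" is marked at baseline 1 (B1) only, and there is no row for functional MRI.

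The text under Outcome measures ends quality-of-life change at week 20. Among the exploratory outcomes it names "the occurrence and change in molecular biomarkers in serum and CSF". The Abstract and the MRI objective in Table 3 speak of changes in brain structure and function.

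**The concern.** A change score needs a measurement at both ends. For three secondary outcomes the article defines the change but does not schedule the second measurement. The article prints both tables in full, so this is a contradiction and not a detail left to a longer document.

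The gap would be complete, not partial. Secondary outcomes are to be analysed in complete cases, which here means no cases, and imputation cannot help where nobody has been measured. A visit that has passed cannot be repeated. For SDMT, the lost time point follows the second course, and the Objective of the trial section presents that phase as the source of insight into repeated pulse treatment. If the outcomes later went unreported, a reader comparing the report with Table 3 could not tell a table error from a selective omission.

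**Working it through.** The article gives no figure to reproduce. The check sets each time point required by Table 3 against the marks in Table 1, taking B2 as baseline, FU1 as week 8, FU2 as week 20 and FU3 as week 52.

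| Instrument | Times needed (Table 3) | Times scheduled (Table 1) | Missing |
|---|---|---|---|
| SDMT | B2, wk 8, wk 20 | B2, wk 8 | wk 20 |
| PROMIS 29 | B2, wk 8, wk 20, wk 52 | B2, wk 8, wk 20 | wk 52 |
| PROMIS Cognitive 4a | B2, wk 8, wk 20, wk 52 | B2, wk 8, wk 20 | wk 52 |
| BDI-II | B2, wk 8, wk 20, wk 52 | B2, wk 8, wk 20 | wk 52 |
| SF-36, FSS, Chalder | B2, wk 8, wk 20, wk 52 | B2, wk 8, wk 20, wk 52 | none |
| MoCA | B2, wk 8, wk 20 | B2, wk 8, wk 20 | none |

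**Changes lost.** SDMT has three defined changes (baseline to 8, baseline to 20, 8 to 20) and loses the last two. Each PROMIS form and the BDI has four (baseline to 8, to 20 and to 52, and 8 to 20) and loses one. By instrument the loss is 2 + 1 + 1 + 1 = 5 of 3 + 4 + 4 + 4 = 15. Table 3 does not say which PROMIS form it means, but both lack week 52, so the answer is the same.

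**Is it a shifted column?** No. Each row has 12 visit cells, and similar rows carry the marks that are absent here: MMQ, SF-36, FSS and Chalder at FU3, and MoCA and the Trail-Making Test at FU2. SF-36 shares its Table 3 row with PROMIS, and FSS and Chalder share theirs with the BDI. In each of those two rows, one part can be computed at week 52 and the other cannot.

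**Does the text settle it?** Not fully.

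- The description of FU3 mentions a telephone interview and questionnaires but does not name them; only Table 1 lists them.
- For PROMIS, the Outcome measures text stops at week 20 and so agrees with Table 1 against Table 3. It is also narrower than both tables for SF-36, which has week 52 in each.
- For SDMT, the same text puts neuropsychological and cognitive scores at week 20, which sides with Table 3.

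**CSF and MRI.** The biomarker row of Table 3 does not name CSF. Diagnostic blood is taken at B2, FU1 and FU2, so that row can be computed from serum. CSF change is named only in the running text, and one optional puncture at B2 cannot yield it. For MRI, the core schedule has one structural scan at B1. Selected patients in the biomarker and diagnostic platform receive additional imaging, and Table 1 marks platform enrolment at B2 and FU1.

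**The case against.** The strongest reply is that these are wording slips in combined rows. Week 52 is right for SF-36, FSS and Chalder, and PROMIS and BDI may simply have been carried along. That is plausible, particularly for PROMIS, where the text agrees with Table 1. It affects which table to correct, but the contradiction remains.

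The reply is also right that little of the main comparison is at risk. Secondary outcomes are exploratory. Weeks 20 and 52 both fall after the open phase in which everyone is offered methylprednisolone. SF-36, FSS and Chalder still cover quality of life and fatigue at week 52.

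Three stronger readings are tempting, and the documents do not support them:

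- A reader might infer that CSF change is a Table 3 outcome lost in all 418 patients. Table 3 does not name CSF, and sampling is optional, so 418 was never its denominator.
- A reader might infer that MRI change cannot be computed at all. Table 3 gives its MRI alterations no time point, and the platform may supply later scans. The platform marks show enrolment, not scan dates, so they establish neither that such scans exist nor when.
- A reader might infer that SDMT was dropped from FU2 by oversight because the whole battery is repeated there. The Wortschatztest and LPS are marked at B2 only, so the schedule does not repeat every test.

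**Conclusion.** The contradiction stands for three secondary outcomes: SDMT at week 20, and PROMIS (both forms) and BDI at week 52. Under Table 1 as printed, these time points have no data in any participant. The conclusion rests on Table 1 being the operative schedule, and the article names no other. The documents do not show which table is in error.

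The consequence is modest. The primary outcome, its week-8 comparison and all week-8 secondary comparisons can be computed as planned. What would be lost is the SDMT result after the second treatment phase and the long-term PROMIS and mood results.

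The CSF and MRI points are minor. They concern wording that promises more than the core schedule delivers, and neither shows that a Table 3 outcome cannot be computed.

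**What to change.** Reconcile Tables 1 and 3 in one of two ways, chosen separately for each instrument:

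1. Add SDMT at FU2, and add PROMIS 29, PROMIS Cognitive 4a and BDI-II to the FU3 questionnaires. The cost is one additional test at an existing outpatient visit and three questionnaires at week 52, a small added burden for patients.
2. Delete week 20 and the week 8 to 20 change for SDMT, and week 52 for PROMIS and BDI, from Table 3. This costs only wording, but those results are given up.

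Either way, bring the quality-of-life time points in the Outcome measures text into line with the tables. If participants have already passed FU2 or FU3, additions will yield data only from later visits; the article should then say so, and the change should be dated.

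Two edits need wording only. Restate CSF as occurrence at baseline, which matches the reference to baseline CSF under Objective of the trial, and limit biomarker change to serum. In the Abstract and Table 3, state that any structural or functional MRI change comes from the platform subgroup only. No further lumbar puncture or scan is needed for either edit.

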### Sample size calculation and statistical analysis

For the PoCoVIT trial, we aim to detect an improvement in the MMQ sub-domain memory satisfaction. We consider a change of additional 15 points a clinically relevant improvement. Based on our previous data, we anticipate this improvement in 15% of the verum group and 5% of the placebo group. To achieve 90% power at a significance level of α = 0.05, we require 188 patients in each group. This calculation uses a two-sample test for proportions (z-test with arcsine transformation) in the stats package of the R statistical computing environment (version 4.0.2). Assuming a dropout rate of 10%, our recruitment target is 209 patients per group, ensuring that 188 participants remain after dropout. We, therefore, plan to screen 700 patients to enrol the necessary 418, stratified by sex, age, and MoCA score.

Since a single primary outcome is selected, no multiplicity adjustment is required. Analyses of secondary outcomes will be exploratory. For the primary outcome, a binary logistic regression model will be used, focusing on improvement in outcome variables and treatment group as main effects, adjusting for stratification variables. Odds ratios will be reported with 95% confidence intervals, and an alpha of 0.05 has been set for significance. Complete case analysis will be conducted. Where missing values exceed 5%, sensitivity analysis will be performed using multiple imputation chain equations [4].

Secondary outcomes will be initially analysed descriptively and modelled using appropriate techniques such as ANCOVA and logistic models, depending on the outcome distributions. The treatment variable will be included as the main factor adjusting for stratification variables similar to the primary analysis model. Treatment effects will be calculated with two-sided 95% confidence intervals, and outcomes will be analysed in complete cases analyses. Safety, subgroup and interim analyses will be conducted. Statistical analyses will be performed using SAS release 9.2 or higher (SAS Institute Inc., Cary, North Carolina, USA) and R (www.r-project.org) version 4.1.2 or higher.

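### The primary logistic model leaves out baseline MMQ memory satisfaction, the score from which the responder endpoint is calculated: a modest loss of efficiency and robustness, not an error

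*Protocol article*

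**What the plan says.** Under Outcome measures, the article defines the endpoint from one scale measured twice: "The primary outcome measure is the intra-patient change in the MMQ sub-domain memory satisfaction, demonstrating an increase of" at least 15 points between baseline and week 8. Under Sample size calculation and statistical analysis, the primary model is a binary logistic regression, "focusing on improvement in outcome variables and treatment group as main effects, adjusting for stratification variables".

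Arms and intervention lists the stratification variables: "Participants will be stratified based on age" (cut at 50 years), sex, and MoCA at Baseline 2 (cut at 26 points). Baseline MMQ memory satisfaction is neither a stratification factor nor a named covariate, and no other section adds it. Table 1 places the MMQ at Baseline 2, and the trial description puts the assessments of that visit before randomisation.

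For secondary outcomes, the article offers ANCOVA and logistic models as examples and adds: "The treatment variable will be included as the main factor adjusting for stratification variables similar to the primary analysis model".

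**The concern.** The outcome is the week-8 score minus the baseline score, cut at 15 points. Unless the two scores are almost perfectly correlated, or their SDs differ in an offsetting way, patients with low baseline scores are more likely to reach the cut, through regression to the mean alone. MoCA is a different instrument, split in two, and cannot be assumed to carry this information.

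A prognostic covariate that is already collected is therefore unused. Two things are at stake: some power, and protection of the primary odds ratio against a chance difference between arms in baseline score. Because the article states the covariate set, this is a choice that can be improved and not a detail left to an unseen analysis plan.

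**Working it through.** **1. The plan's own figure.** Inputs: "we anticipate this improvement in 15% of the verum group and 5% of the placebo group", 90% power, and "an alpha of 0.05 has been set for significance" (taken as two-sided). Pooled two-proportion z-test:

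n = [1.960·√(2·0.10·0.90) + 1.2816·√(0.15·0.85 + 0.05·0.95)]² / 0.10² = (0.8315 + 0.5361)² / 0.01 ≈ 187.05, rounded up to 188.

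This agrees with "we require 188 patients in each group". Dropout: 188/0.90 = 208.9, so 209. (The article names a "two-sample test for proportions (z-test with arcsine transformation) in the stats package". The arcsine formula gives 177.2, so 178. That is a separate matter and does not affect this point.)

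**2. Information available.** Expected responders: 188·0.15 + 188·0.05 = 28.2 + 9.4 = 37.6.

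**3. Link between baseline and change.** With equal SDs and baseline to week-8 correlation ρ, corr(baseline, change) = −√((1−ρ)/2). This gives −0.55 at ρ = 0.4, −0.50 at 0.5 and −0.32 at 0.8. The article gives neither ρ nor an SD, so these are assumptions.

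**4. Power with and without baseline.** Two simulation set-ups, each with 188 per arm, 5% and 15% responders, three binary stratification factors, a Wald test and 3,000 trials per setting.

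*Scores simulated directly (assumed mean 35, SD 12, entry at 50 or below):*

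| ρ | Without baseline | With baseline |
|---|---|---|
| 0.4 | 91.0% | 94.1% |
| 0.5 | 90.5% | 93.0% |
| 0.8 | 91.0% | 91.7% |

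Type I error was 0.040 for both models. At ρ of 0.5 to 0.7, the placebo responder rate falls from about 9–11% in the lowest baseline tertile to 1–2% in the highest.

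*Latent change with correlation −r to baseline:*

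| r (equivalent ρ = 1 − 2r²) | Without baseline | With baseline |
|---|---|---|
| 0.2 (0.92) | 90.9% | 91.2% |
| 0.3 (0.82) | 91.0% | 92.1% |
| 0.4 (0.68) | 90.5% | 91.9% |
| 0.5 (0.50) | 91.2% | 93.9% |
| 0.6 (0.28) | 91.0% | 95.0% |

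Type I error with 10% responders in both arms: 0.047 without and 0.048 with baseline at r = 0.3; 0.055 and 0.056 at r = 0.5. The simulation standard error of one power figure is √(0.91·0.09/3000) ≈ 0.5 points.

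**5. Chance imbalance.** The SD of the standardised baseline difference is √(2/188) = 0.103. So P(|d| > 0.1 SD) = 2[1 − Φ(0.97)] ≈ 33%, and P(|d| > 0.2 SD) = 2[1 − Φ(1.94)] ≈ 5%. Fixing the difference at 0.2 SD with r = 0.5 (1,500 trials each):

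| Baseline of verum arm | Power without | Power with | Null rejection without | Null rejection with |
|---|---|---|---|---|
| 0.2 SD higher | 0.78 | 0.93 | 0.075 | 0.051 |
| 0.2 SD lower | 0.97 | 0.92 | 0.059 | 0.051 |

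The null rows should be symmetric; the gap between 0.059 and 0.075 is compatible with simulation error.

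**The case against.** The strongest reply is that nothing here is wrong. Logistic regression adjusted for the stratification factors matches the randomisation, holds its type I error on average and delivers the planned power. The nominal test already allows for chance imbalance across all randomisations. The gain from baseline is small and rests on correlations that the article does not report; at r of 0.2 or less it is negligible. The power of 0.78 belongs to one direction of a 0.2 SD difference, about 2.5% of trials, and in the other direction the unadjusted model has more power. In the direct-score set-up, a 0.2 SD imbalance moves the placebo rate only from 5% to about 5.7–6.0%. The covariate also has a price: the odds ratio becomes conditional on baseline, and a term linear on the logit scale is one more assumption with about 38 events.

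Most of this stands, and it limits the point to an improvement. It does not remove the case for making it. The gain is available without new data, and a baseline difference can be handled cleanly only if the covariate was named beforehand. The price is small: the present odds ratio is already conditional on three factors, and one coefficient is added.

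A reader might also infer that the secondary ANCOVAs omit the outcome's own baseline. The text does not support that. It names ANCOVA as an example for outcomes declared exploratory, gives no closed covariate list and does not exclude baseline, which an ANCOVA of change ordinarily carries.

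**Conclusion.** The point holds as a modest weakness. The primary model, as stated, omits the baseline value of its own endpoint. Under assumed baseline to week-8 correlations of 0.4 to 0.8, including it adds about 1 to 3 points to a power that is already about 90–91%, with type I error near 0.05 either way. It also removes the dependence of the result on a chance baseline difference, which exceeds 0.1 SD in about a third of trials and 0.2 SD in about one in twenty.

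Two stronger readings should be resisted. One is that the primary analysis is invalid or underpowered; the calculations show that it is neither. The other is that baseline MMQ is the variable most closely tied to a 15-point gain, or that high scorers have no room to rise. The link to baseline follows from how the endpoint is built, but the article gives no correlation, no comparison with other predictors and no scale maximum. The omission itself is certain; the size of its effect depends on the assumptions above.

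**What to change.** Prespecify, before unblinding, that the primary logistic regression includes Baseline 2 MMQ memory satisfaction as a continuous covariate, beside treatment, age group, sex and MoCA group. State that the reported odds ratio is then conditional on baseline as well as on the stratification factors, so it is not directly comparable with one from the present model.

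For secondary outcomes analysed as change, confirm in a phrase that each ANCOVA includes that outcome's own baseline value.

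The cost is one or two sentences and one degree of freedom. No new data are needed. No further patient is lost from the complete-case analysis, because anyone with a week-8 change has a baseline score. The sample size can stay as it is. Timing matters: if baseline is added only after an imbalance has been seen, the adjustment will look data-driven.
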